## **Sample size considerations**

Since we are including our total sample frame, a sample size estimation at the cluster level is not required. However, if we succeed to enroll 50 participants per shelter from 8 shelters (n=400), and the detection rate is 3 times higher in the intervention groups (0.15) than in the comparator groups (0.05), we will have 90% power to detect a statistically significant and clinically important difference at a type I error rate of alpha=0.05 (one tailed), assuming an intraclass correlation of ~0.008. These computations were done using WinPEPI, and informed by conservative estimates from other studies on respiratory illness in the homeless (4, 5).

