## **Study Design**

We are conducting a prospective random cluster-allocation study to compare the effectiveness of four different surveillance regimens across eight shelters in Hamilton (four men’s and four women’s shelters). The shelters are associated with Good Shepherd, Mission Services, Wesley Urban Ministries, YWCA and Hamilton Native Women’s Centre; all have agreed to work with us on this study. The surveillance methods are as follows:

1. Active daily surveillance of symptoms and testing only symptomatic participants. This is the current standard of care protocol for residents accessing the shelters.
2. Once weekly self-collected oral swabs (OS) regardless of symptoms using written and visual instructions (attached).
3. Once weekly self-collected oral-nares swab (O-NS) regardless of symptoms using written instructions (attached).
4. Once weekly nurse collected nasopharyngeal swab (NPS) regardless of symptoms

[figure not shown]

All participants in the intervention groups will continue to receive active daily surveillance of symptoms. Only participants who provide consent will be considered in the intervention groups and verbal consent will be recorded by study staff at each site. At all sites participants who seek care for respiratory symptoms or symptoms potentially related to COVID-19 would get testing as is routinely done.

Each surveillance regimen will occur for 6-8 weeks based on the funding available. Each shelter has approximately 100 participants and we are aiming to enroll 30-50% of participants at each site.

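### The 90% power statement names neither the contrast nor the split of the 400; with two shelters per regimen, power is about 77–79% pooled and 64–67% per regimen on normal theory

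*Protocol*

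**What the plan says.** The Protocol, under Study Design, sets out to "compare the effectiveness of four different surveillance regimens across eight shelters in Hamilton". The first regimen is daily symptom screening with testing of symptomatic residents only: "This is the current standard of care protocol for residents accessing the shelters". The other three add weekly swabs, taken in three different ways. Under Outcomes, the primary outcome is counted separately for each arm.

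Under Sample size considerations there is one power statement. Its condition is "if we succeed to enroll 50 participants per shelter from 8 shelters (n=400" participants, its effect is that "the detection rate is 3 times higher in the intervention groups (0.15) than in the comparator groups (0.05", and its conclusion is "we will have 90% power to detect a statistically significant and clinically important difference at a type I error rate of alpha=0.05 (one tailed". The intraclass correlation is taken as about 0.008, and the software is named. The section does not say how many of the 400 stand on each side or whether the three swab regimens are pooled. It gives no separate figure for a single regimen.

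**The concern.** The power statement describes two sides with one rate each, whereas the design has four regimens of which only one is standard of care. Equal halves of the 400 do not correspond to any comparison with standard of care if the eight shelters are spread evenly over four regimens. Control would then be a quarter of the sample, and a single swab regimen another quarter.

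This affects how the results will be read. A reader who takes 90% at face value would treat a null result for a swab regimen as having a 10% chance of missing a true three-fold difference. On the per-regimen contrast that chance is about one in three, and on the pooled contrast it is a little over one in five.

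**Working it through.** **Inputs from the Protocol.** Rates 0.15 and 0.05, 50 per shelter, eight shelters, one-sided alpha 0.05 and intraclass correlation 0.008 (Sample size considerations). Four regimens, one of them standard of care (Study Design).

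**Assumption.** Two shelters per regimen (8 / 4). The text does not state it, and the design figure is not shown.

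**Design effect.** 1 + (50 − 1) × 0.008 = 1.392. Effective sizes: 200 / 1.392 = 143.7; 300 / 1.392 = 215.5; 100 / 1.392 = 71.8.

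**Formula.** With effective sizes m0 (control) and m1 (intervention), and overall rate p̄ weighted by size:

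- SE0 = √[p̄(1 − p̄)(1/m0 + 1/m1)]
- SE1 = √[0.05 × 0.95/m0 + 0.15 × 0.85/m1]
- Power, pooled null variance = Φ[(0.10 − 1.645 × SE0) / SE1]
- Power, unpooled variance = Φ[0.10 / SE1 − 1.645]

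**Step 1: the stated figure.** For 200 v 200, p̄ = 0.10, SE0 = 0.0354 and SE1 = 0.0349, so power = Φ(1.20) = 88.4% (unpooled 88.9%). A beta-binomial simulation with the same intraclass correlation gives 90%, and exact enumeration at 144 v 144 gives 90.3%. The stated figure is therefore correct for this split. A two-sided test (81.0%) and no design effect (95.7%) do not reproduce it.

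**Step 2: the contrasts with symptom-only surveillance.**

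| Contrast (shelters) | p̄ | SE0 | SE1 | Pooled formula | Unpooled formula | Simulated, pooled test |
|---|---|---|---|---|---|---|
| 300 v 100 (6 v 2) | 0.125 | 0.0451 | 0.0354 | Φ(0.73) = 76.8% | Φ(1.18) = 88.1% | 79% |
| 100 v 100 (2 v 2) | 0.10 | 0.0501 | 0.0494 | Φ(0.36) = 64.0% | Φ(0.38) = 64.8% | 66% |

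Exact enumeration of the pooled test gives 80% at effective 216 v 72 and 66.5% at 72 v 72.

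**Step 3: does the unpooled test hold its level at 6 v 2?** With no difference between the sides, its simulated one-sided rejection rate is 8.9% when both rates are 0.05 and 7.2% when both are 0.125. Its simulated power is 86%. The pooled test rejects 3.8% and 4.2% of the time. The 88% is therefore not power at the stated 5%.

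**Step 4: few clusters.** The figures above use normal theory with a known intraclass correlation. A simulated equal-variance t-test on shelter proportions gives about 65% at 6 v 2 (6 df) and about 41% at 2 v 2 (2 df). Putting the t quantile into the unpooled formula gives 80% and 39%. The 6 v 2 figure thus depends on how the variance is estimated, while the 2 v 2 figure hardly does.

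**Step 5: detectable rates.** Solving the pooled formula for 80% power against 0.05 gives about 0.155 for 300 v 100 and about 0.18 for 100 v 100.

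**Step 6: enrolment.** Fifty per shelter is the top of the 30–50% target under Study Design. At 30 per shelter the design effect is 1 + 29 × 0.008 = 1.232, and the pooled formula gives 59% (6 v 2) and 50% (2 v 2).

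**The case against.** The strongest reply is that the sentence may refer only to pooled swabbing against standard of care, with the right 3:1 split entered into an unpooled formula. That gives 88%, as close to 90% as the equal split does. The protocol names the software but not the formula, so this cannot be excluded. A reader might infer that the planners divided 400 by two; the documents do not show this, and the plural in "than in the comparator groups (0.05" may simply mean the control shelters. The reply does not save the figure, because the unpooled test exceeds the 5% level that the same sentence claims.

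Second, two shelters per regimen is an inference. This stands, and the verdict is conditional on it. An uneven allocation with four control shelters would permit 200 v 200 for pooled swabbing. It would leave four shelters for three swab regimens, so no single regimen would have 200, and nothing in the text suggests it.

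Third, the protocol never claims 90% for a single regimen. A reader might infer such a claim, but the wording does not make it. The 64–67% therefore does not contradict the sentence. It shows that the sentence does not cover the comparison that Study Design and Outcomes describe. The choice of confirmatory contrast may be left to an analysis plan, but a power figure printed in the protocol still has to belong to an identifiable contrast.

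Finally, the calculation did not set the number of shelters, because the whole sampling frame is included. That limits the consequence to interpretation: nothing here shows that enrolment must rise.

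**Conclusion.** The point holds in this form: the 90% is attached to no named contrast or split, and it overstates the power of the contrasts available under an even allocation.

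- **Pooled swabbing v symptom-only (300 v 100):** about 77–79% on normal theory with a test that holds 5%, and about 65% with a cluster-level t-test.
- **One regimen v symptom-only (100 v 100):** about 64–67% whether the z-test variance is pooled or unpooled, and about 41% with a cluster-level t-test.

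These figures rest on two shelters per regimen, 50 enrolled in every shelter, the protocol's rates and intraclass correlation, and no adjustment for three comparisons. Splitting alpha over three would take the per-regimen figure to about 45% on normal theory. The per-regimen result is the firmer of the two, since the pooled one varies more with the formula.

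**What to change.** In Sample size considerations:

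1. Name the contrast to which the power statement refers, and state how many shelters and participants stand on each side.
2. Replace 90% with the power of that contrast under the planned test. With two shelters per regimen this is about 77–79% for pooled swabbing and about 64–67% for each regimen on normal theory. Give the cluster-level figures alongside (about 65% and 41%), so that one overstated power is not replaced by another.
3. Add the detection rates detectable with 80% power against 0.05: about 0.155 pooled and 0.18 per regimen, marked as pooled-variance normal-theory values.

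If the actual allocation is not two shelters per regimen, redo the figures with the true split. Leave the number enrolled as it is. The change is to protocol wording only, and its downside is a less favourable stated power.

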## **Inclusion Criteria:**

1. Willing and able to provide verbal consent to participation in the study.
2. Male or female > 18 years of age, residing in one of the homeless shelters within Hamilton, ON.

## **Exclusion Criteria:**

1. Unable or unwilling to give consent.
2. Male or female < 18 years of age.

## **Data Collection Methods**

1. COVID-19 swab results will be processed as per usual protocol by the Virology Research Lab at St. Joseph’s Healthcare (SJH)

Specimens identified as positive in the research lab will be directed to the Clinical Virology Lab within HRLMP for confirmatory testing.

1. All swabs were placed into a viral inactivation medium and transported to the laboratory for COVID-19 testing. Briefly, total nucleic acid was extracted from specimens and then amplified by RT-PCR for the UTR and Envelope genes of SARS-CoV-2 and the human RNase P gene, which is used as a sample adequacy marker.

